### Sample size estimation

2.5

The G∗Power program [65] was utilized to determine the sample size. The program's objectives included three groups, three assessments, four covariates (depression, anxiety, adjustment, and attitude toward internet-based interventions score), a medium effect size (Cohen's *d* = 4, Cohen's *f* = 2), a power of 80 %, and a significance level of *p* = 0.05. Therefore, a minimum sample size of 244 individuals is needed to detect a significant difference.

It is important to consider dropout rates while determining the sample size. Based on their review from the studies between 1990 and 2009, Melville et al. [37] found that the dropout rates range from 2 to 83 %, with an average rate of 31 % in internet-based interventions. Another meta-analysis by Meyerowitz-Katz and colleagues [38] reported the average attrition rate in internet-based interventions as 43 % in studies published in between 2011 and 2019. Based on the previous research (also see Ref. [66,67]), a 35 % dropout rate is anticipated for this study. The dropout rates for internet-based interventions are comparable to those in previous studies based on traditional counseling interventions [68], in their meta-analysis, reported that 55 % of total participants completed the internet-based treatments.

In light of the power analysis calculated through G∗power software, it is suggested that each group should contain 81 people. Due to our expectation of a 35 % dropout rate, an additional 30 participants will be added to each group.

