### Aims

1.2

This study aims to accomplish two main objectives. The initial goal is to test the effectiveness of the internet-based intervention for university students, UNIPDES, which is based on a transdiagnostic CBT, in raising psychological adaptation levels and improving the depressive and anxiety symptoms in university students, controlling for participants' initial depressive symptoms, anxiety, psychological adjustment scores, and attitudes toward internet-based interventions. Consistent with this objective, we seek to evaluate the variations between guided and unguided treatment delivery compared to the waiting list control group.

The second goal is to assess the reasons why users who enroll in internet-based interventions dropout. In order to assess the possible influence of participant attitudes on internet-based therapies on dropout rates, we want to incorporate an analysis of these attitudes into our study. In particular, knowing how people's attitudes, whether favorable or unfavorable, affect their choices to stick with or stop using such interventions can help a researcher to improve their design and execution. Our study aims to add to the body of knowledge on dropout in internet-based interventions in this regard.

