### Statistical analyses

2.10

A Mixed ANOVA will be employed to analyze the data, with Group (Guided, Unguided, Control) as the between-subjects factor and Time (Baseline, Post-Test, Follow-Up) as the within-subjects factor. This approach will assess both the main effects of Group and Time, as well as the interaction effect between Group and Time on the primary outcomes—changes in depression, anxiety, and adjustment levels. Post-hoc tests will be conducted to explore significant interactions. If necessary, covariates will be included in the analysis through a Mixed ANCOVA to adjust for baseline differences.

Dropout and missing data are anticipated in the study. To address this, missing data will be handled using relevant methods, e.g., multiple imputation or Multilevel Mixed-Model Regression Analysis, depending on the nature and pattern of missingness. Multiple imputation will be employed to estimate missing values if the data are missing at random, while Multilevel Mixed-Model Regression Analysis will be applied to account for both missing data and repeated measures over time. Baseline characteristics across the three groups will be tested using statistical methods such as t-tests, chi-square tests, or ANOVA to ensure comparability. Any significant differences will be adjusted for in subsequent analyses. These approaches will help ensure the robustness of the findings despite anticipated dropout and missing data.

The qualitative data will be transcribed and coded into themes by two independent researchers to ensure reliability. In the analysis of the data, the MAXQDA program will be utilized. According to the principles of [81] to ensure the reliability and validity of the results, the coding and assignment of themes will be conducted by several researchers, and the evaluation will be made through consensus/(disagreement + agreement) ∗100 formula as suggested. At the end of the analysis, consensus and disagreements will be evaluated in a project team meeting.

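### The sample size section prints effect sizes that cannot give N = 244, and its 80% power is not the power of the planned Group x Time test or of the arm comparisons

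*Protocol article*

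**What the plan says.** The Protocol article, section 2.5 (Sample size estimation), reports a G*Power calculation for "three groups, three assessments, four covariates", with "a medium effect size (Cohen's *d* = 4, Cohen's *f* = 2", 80% power and "a significance level of *p* = 0.05". It concludes that "a minimum sample size of 244 individuals is needed to detect a significant difference", which becomes 81 per group before the allowance for dropout. The section does not name the G*Power procedure and gives no correlation between repeated measures.

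Section 2.10 (Statistical analyses) plans a 3 x 3 mixed ANOVA whose tests include "the interaction effect between Group and Time" on depression, anxiety and adjustment, followed by post-hoc tests. Covariates enter only if judged necessary. Section 1.2 (Aims) says "we seek to evaluate the variations between guided and unguided treatment delivery compared to the waiting list control group", and describes the effect as tested while controlling for the baseline scores.

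**The concern.** Three things do not fit together.

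- The printed effect sizes conflict with the label medium and with a requirement of 244 people.
- The inputs name three assessments, as a repeated-measures calculation would, but there is no within-person correlation, which the usual repeated-measures procedure needs.
- The test that 244 appears to belong to is not the one section 2.10 plans.

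The sample size is the main quantitative justification of the trial. As printed, a reader cannot reproduce it. The reader may also take the 80% as the power of the Group x Time test, or as the power to detect 0.4 SD between any two arms. The calculation supports neither.

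**Working it through.** Inputs from section 2.5: three groups, three assessments, four covariates, power 80%, alpha 0.05, N = 244, 81 per group. Assumed here because the article is silent: the correlation rho between repeated measures, and the pattern of effects across arms.

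**1. The stated figure.** For a one-time-point omnibus F test, the noncentrality is lambda = N f², with df1 = 2 and df2 = N − 3 − q for q covariates.

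- With f = 0.2, q = 4 and N = 244: lambda = 244 × 0.04 = 9.76, df2 = 237, power 0.8001. At N = 243 power is 0.7984, so 244 is the exact minimum.
- With q = 0, 1, 2 or 3 the minimum is again 244. The match identifies f = 0.2 and 2 df, but cannot show how many covariates were entered.
- With f = 2 as printed, q = 4 and N = 10: lambda = 10 × 4 = 40, df2 = 3, power 0.88. Ten people would be enough.

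**2. Group x Time at f = 0.2.** G*Power's default for the within-between interaction uses lambda = f² N m/(1 − rho), with m = 3, df1 = 4 and df2 = 2(N − 3).

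| rho | N for 80% power |
|---|---|
| 0 | 102 |
| 0.3 | 73 |
| 0.5 | 53 |
| 0.7 | 33 |

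The two alternative effect-size conventions in G*Power give about 155. Setting lambda = N f² with 4 df gives just over 300. The between-group main effect over three assessments gives from 84 (rho = 0) to about 213 (rho = 0.8). None of these gives 244.

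**3. Power of the planned interaction test.** The direction depends on what f means and on rho.

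- If 0.2 is the interaction f under the G*Power default, power at N = 243 is above 99% for rho from 0 to 0.7.
- Suppose instead that both programs differ from waitlist by 0.4 SD at T1 and T2 and by nothing at baseline, with SD 1 and compound symmetry. The squared interaction effects sum to 0.0711, and lambda = 81 × 0.0711/(1 − rho). This gives 8.23, 11.52 and 19.2 at rho = 0.3, 0.5 and 0.7, and power of 61%, 78% and 95%.

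**4. The pairing of d with f.** f = d/2 holds for two equal groups. With three arms, f is the SD of the three means.

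- Means of 0.4, 0.4 and 0 give f = 0.4 × √(2/9) = 0.189. At N = 244, lambda = 244 × 0.0356 = 8.68, and omnibus power is 75%.
- In reverse, f = 0.2 means a largest arm difference of 0.2/√(2/9) = 0.42 SD when two arms are equal, or 0.2 × √6 = 0.49 SD when one arm lies midway.

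**5. A two-arm comparison at d = 0.4, 81 per arm, two-sided alpha 0.05.**

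- Unadjusted: noncentrality 0.4 × √(81/2) = 2.55, power 72%.
- Adjusted for baseline at an assumed correlation of 0.5: 2.55/√(1 − 0.25) = 2.94, power 83%.

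**The case against.** Four replies carry weight.

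- **The misprint is obvious.** The word medium and the figure 244 both point to d = 0.4 and f = 0.2, and large values are not mathematically impossible. That is right. The printed values are incompatible with 244, and the intended ones are easily guessed. They still need correcting: the same sentence prints 0.05 intact, so a decimal lost in text extraction is unlikely.
- **The procedure is not known.** Section 2.5 names no test, so the single-time-point reading rests on a numerical match that holds for any number of covariates from 0 to 4. This also stands. Only the authors can say what they ran.
- **A reader might infer that the planned analysis is underpowered.** The document does not support this. Depending on rho and the effect pattern, Group x Time power lies well below or well above 80%.
- **A reader might also infer that 80% power at d = 0.4 between arms is missed even without dropout.** This holds for an unadjusted comparison only. Section 1.2 speaks of controlling for baseline scores, and with a baseline correlation of 0.45 or more the two-arm power exceeds 80%. The article does not say which SD d refers to.

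The article gives no expected difference between guided and unguided delivery, so any power figure for that contrast would rest on a reviewer's assumption. How alpha is shared over the three outcomes, and which time point leads, may be settled in an analysis plan not shown here. Neither carries this point.

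**Conclusion.** The point holds in limited form. The printed effect sizes are wrong for N = 244 by a factor of ten, judged by the f that reproduces it. The listed three assessments did not enter any usual calculation that gives 244. The 80% belongs, by inference, to an omnibus three-group test at one time point with f = 0.2, and not to the Group x Time test or to any arm comparison.

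The misreading of d as 0.4 in a three-arm design is modest: omnibus power falls from 80% to 75% if both programs achieve 0.4 SD. Power for one program against waitlist at that difference is 72% or about 83%, depending on baseline adjustment. These figures assume equal arms of 81, complete data and alpha 0.05 for a single outcome. What is established is a power statement that does not match the plan. A shortfall in the planned analysis is not established.

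**What to change.** In section 2.5:

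1. Correct the effect sizes, apparently to d = 0.4 and f = 0.2, after checking the original G*Power output.
2. Name the G*Power procedure actually run, and remove any listed input that it did not use.
3. State that with three arms f = 0.2 corresponds to a largest difference between arms of about 0.42 to 0.49 SD.
4. Either say that the 80% applies only to the omnibus test at one time point, or recompute and report power for the planned Group x Time test and for each program against waitlist, showing the assumed correlation and effect pattern.

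The cost is a rewritten paragraph and a short calculation. This point requires no change in recruitment or design, though the stated power may become less favourable.

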## Abstract

University students often face significant mental health challenges, including depression, anxiety, and difficulties in adjustment, which can be exaggerated by the demands of independent living and increased life responsibilities. These challenges are often compounded by barriers to seeking help, such as stigma and limited access to university resources, which can further deteriorate students' well-being. This protocol was created to assist college students in overcoming these obstacles and to assess, in comparison to a control group, the impact of a guided and unguided online intervention platform based on transdiagnostic CBT (UNIPDES) on depression, anxiety, and adjustment levels. The calculated sample size for the study will include 330 students, and the participants will be selected from five different universities located in Türkiye. Participants will be randomly assigned to either guided, unguided, or control groups. Guided and unguided group participants will receive six weeks of intervention, and the waitlist control group will receive the unguided version of the program after twelve weeks of randomization. Assessments will take place at baseline, post-test (8 weeks post-baseline) and follow-up (12 weeks post-baseline). A Mixed ANOVA will be employed to analyze the data, with Group (Guided, Unguided, Control) as the between-subjects factor and Time (Baseline, Post-Test, Follow-Up) as the within-subjects factor, as well as to assess the interaction effect between Group and Time on the primary outcomes—changes in depression, anxiety, and adjustment levels. Additionally, students’ reasons for dropout will be assessed qualitatively. The results from this study can build evidence for the effectiveness of transdiagnostic guided and unguided internet-based intervention for treating depression, anxiety, and adjustment problems of students. UNIPDES can provide a flexible, easy-to-access, and cost-effective treatment for the problems that students commonly face. Trial registration is registered at ClinicalTrials.gov Protocol Registration and Results System (Trial number: NCT06245200).

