This study has several foreseen limitations. First, the study sample will include students from selected universities located in Türkiye and is thus not representative of the general population. Another expected limitation is the sample size. Considering the possibility of a 35 % dropout rate, a larger sample size was targeted to meet the requirements needed to evaluate the effectiveness of the program. Even if the required sample size is possible to obtain, in cases of lower rates of participation, the program will be announced to students studying at different Turkish universities as an alternative. A similar plan will be followed in case the dropout rates increase more than expected (35 %). The study's use of a waiting control group constitutes another drawback. It may be more difficult to verify that the treatment alone will be the cause of the outcome because of some external factors (i.e., time, changes in life conditions) that may obscure the treatment's effectiveness. Similarly, using a control group may lead to overestimating the treatment effects, particularly due to minor improvements observed in the symptoms of participants in the control group condition [82].

Additionally, the study has several strengths. First off, most past studies (both globally and in Turkey) on internet-based interventions tended to concentrate on the treatment of particular problem areas [[45], [47], [48], [49]]. The intervention program will make use of the transdiagnostic approach (TA), which gives professionals the flexibility to target multiple problem areas instead of a single one. Even though the TA has received a lot of attention, no prior research has been done to evaluate its effectiveness in a self-help program. Thus, the use of a TA, which enables interventions to reach a wider range of problem areas, is another strength of this study. Lastly, the acceptability and usability of these interventions were neglected in earlier research assessing the effectiveness of internet-based self-help programs. Though it is well known that the main problem with internet-based therapies is premature termination (e.g., Ref. [68]), early dropout has been a significant worry that is often disregarded. As a result, this study's ability to pinpoint the causes of early user dropout will help guide future research on ways to improve the acceptability and usability of internet-based interventions.

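### The dropout allowance is too small for the plan's own 35%: 330 enrolled leaves about 214 against a stated minimum of 244, so the total covers only about 26% dropout

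*Protocol article*

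**What the plan says.** Section 2.5 (Sample size estimation) describes a G*Power calculation with "three groups, three assessments, four covariates", "a medium effect size (Cohen's *d* = 4, Cohen's *f* = 2"), 80% power and "a significance level of *p* = 0.05". It concludes that "a minimum sample size of 244 individuals is needed to detect a significant difference". Further on, "it is suggested that each group should contain 81 people", and because 35% dropout is expected, "an additional 30 participants will be added to each group".

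The Abstract gives the enrolment total: "The calculated sample size for the study will include 330 students".

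The Discussion, under limitations, presents the enlarged target as having been set with 35% dropout in mind. It offers a wider announcement to other Turkish universities if participation is low, and adds for dropout: "A similar plan will be followed in case the dropout rates increase more than expected", with 35% given as the expected level.

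**The concern.** Dropout is a fraction of those enrolled. If 244 are to remain after 35% leave, the enrolled number must be 244 divided by 0.65. An addition of 30 to 81 is 37% of the 81 required, but only 27% of the 111 enrolled. It looks as though the percentage was applied to the wrong base.

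If so, the trial falls short of its own minimum when dropout is exactly as expected, with no need for a pessimistic scenario. The Discussion then tells the reader that 35% has been provided for when it has not, and its dropout contingency starts only above 35%, after the shortfall has already arisen.

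**Working it through.** **Inputs.** From 2.5: required N 244; 81 per group; three groups; four covariates; alpha 0.05; power 80%; expected dropout 35%; 30 added per group. From the Abstract: 330 enrolled.

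**Step 1: reproduce 244.** The effect sizes are printed as d = 4 and f = 2. An f of 2 would need only a handful of participants, so I assume lost decimal points: d = 0.4, f = 0.2. For the ANCOVA F test of the group effect:

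- df1 = 3 − 1 = 2; df2 = N − 3 − 4; noncentrality λ = N f²
- power = P(F′(df1, df2, λ) > F(0.95; df1, df2))
- N = 244: df2 = 237, λ = 244 × 0.04 = 9.76, power = 0.8001
- N = 243: λ = 9.72, power = 0.798

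So 244 is the smallest N that reaches 80%, and the stated figure is reproduced. Leaving out the covariates also gives 244. Other choices do not: f = 0.25 gives 158 and f = 0.4 gives 64. With an assumed correlation of 0.5 between assessments, the repeated-measures between-group test at f = 0.2 gives 164. The Group × Time test gives 53 at f = 0.2 and 202 at f = 0.1.

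**Step 2: reproduce the enrolment total.**

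- 244 × 1.35 = 329.4, rounded up to 330 (the Abstract's figure)
- 3 × (81 + 30) = 3 × 111 = 333 (the figure implied by 2.5)
- 3 × 81 = 243, one short of 244

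**Step 3: what remains at 35%.**

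- 330 × 0.65 = 214.5, about 214; short by about 30
- 333 × 0.65 = 216.45, about 216; short by about 28

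This step needs no effect size and no model.

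**Step 4: dropout that the total does cover.**

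- 1 − 244/330 = 26.1%
- 1 − 244/333 = 26.7%

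**Step 5: the allowance for 35%.** 244 / 0.65 = 375.4, so 376. Since 3 × 125 = 375, equal groups need 126 each, or 378.

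**Step 6: power at 35% dropout, same calculation as Step 1.**

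| Remaining N | df2 | λ | Power |
|---|---|---|---|
| 244 | 237 | 9.76 | 0.800 |
| 216 | 209 | 8.64 | 0.746 |
| 214 | 207 | 8.56 | 0.742 |

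**Step 7: the contingency.** The Discussion has two triggers: low participation, and dropout above 35%. With 330 enrolled, dropout between about 26% and 35% puts the trial below 244 and sets off neither. The average of 31% that 2.5 cites from an earlier review lies in that gap: 330 × 0.69 = 227.7, about 227, with power 0.769.

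**The case against.** Three points on the other side carry weight.

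**The power figure belongs to the sizing model.** Section 2.10 plans a Mixed ANOVA with Group × Time over three assessments, with covariates only if needed. Under repeated-measures formulas at N = 214, power would be 0.90 for the between-group test (f = 0.2, correlation 0.5), 0.84 at correlation 0.7, and 0.83 for Group × Time at f = 0.1 and correlation 0.5. The document states no correlation, so these are assumptions. They are enough, though, to block the inference that the planned analysis is underpowered. A reader might draw that inference from the 74%, but the document does not support it.

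**Dropout need not mean missing outcomes.** Section 2.9 sends the 8-week assessment to everyone, including those who did not finish the programme, and 2.10 plans multiple imputation or a mixed model. Section 2.9.2.5 uses dropout for people who stop using the platform. So 214 is the count if every dropout is lost, and some may still supply data. For the same reason, the 55% treatment completion cited in 2.5 should not be turned into an analysed sample. Even so, the plan itself enlarges the sample for dropout and puts no figure on what would be recovered, so the allowance is still wrong on its own terms.

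**The contingency has a second trigger.** A reader might take extra recruitment to depend on dropout above 35% alone. Low participation also starts it. Neither trigger is set off by dropout of 26% to 35% in a fully recruited trial.

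**Conclusion.** The point holds as an arithmetic error. A requirement of 244 with 35% dropout needs 376 enrolled; 330 (or 333) covers about 26% (27%) and leaves about 28 to 30 fewer than the stated minimum at the plan's own expected rate. This rests only on figures printed in the article.

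The loss of about 6 percentage points of power, from 80% to about 74%, is conditional. It assumes f = 0.2 in place of the printed 2, the ANCOVA that reproduces 244, and every dropout counted as lost. It shows that the stated sizing does not deliver its stated power at the stated dropout rate, and says nothing definite about the Mixed ANOVA. The mismatches of 330 with 333 and of 243 with 244 are rounding matters to tidy in the same edit.

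**What to change.** Keep recruitment as planned and correct the text.

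- Use one enrolment total, 330 or 333, in the Abstract and in 2.5.
- Reconcile 81 per group with 244, since three groups of 81 make 243.
- In 2.5, state that this total keeps 244 participants only up to about 26% dropout (27% for 333), and that at the expected 35% the stated calculation gives about 74% power. Name that calculation and its effect size, with the decimal points confirmed.
- In the Discussion, correct the statement that the enlarged target accommodates 35% dropout.

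For information, holding 80% at 35% dropout would take 376 participants, or 378 in equal groups of 126, which is 46 to 48 more than 330. That would be a change to recruitment and is not needed for the correction. Lowering the dropout trigger to 26% is not a wording change either: with 35% expected, it would be expected to fire.

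The cost of the correction is a slightly less favourable stated power.
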